## 15 DATA ANALYSIS AND STATISTICAL METHODS

### 15.1 Statistical Methods

#### Analysis populations

It is planned that the statistical analysis involves four patient populations:

- All subjects enrolled in the study (**FAS, full analysis set**). This population will be used to describe the basic characteristics, including demographics and anthropometric parameters of patients, data on the underlying and concomitant diseases.
- The safety analysis will include all patients who received at least one dose of the investigational product. This population will also be used to assess primary efficacy parameters. In this case, the patient's group will be determined by the "intention to treat" (**ITT analysis**).
- Additionally, analysis of secondary efficacy parameters will be performed in all subjects who completed the study without any significant Protocol deviations (**PP analysis**).
- The population for the pharmacokinetic analysis will consist of patients for whom data were obtained at least at one time point of the PK measurement plan.

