### **1.3.2 Findings of Phase I Clinical Study of Tigerase**

A single-center, open-label, randomized comparative phase I study (No.KI 39/14 (KI 39/14)) was conducted to assess the safety, tolerability, and pharmacokinetics of Tigerase (GENERIUM JSC, Russia) and Pulmozyme® (F. Hoffman-La Roche, Switzerland) on multiple 2.5 mg dose inhalation in healthy volunteers.

Fifty volunteers enrolled in the study inhaled the medicinal product Pulmozyme® (Group I) or Tigerase (Group II) in accordance with randomization at a dose of 2.5 mg per day for 5 days. The follow-up period of volunteers after the product inhalation was 5 days. The assessment of safety

parameters considered: incidence of adverse events, deviations in physical examination findings; vital signs, laboratory parameters, ECG data, peak flowmetry and spirometry (forced expiratory volume in 1 second (FEV1) and forced vital capacity (FVC)).

The plasma concentration of dornase alfa was assessed in the study. Since the total level of dornase alfa is composed of the endogenous level and the level of active ingredient dornase alfa of the administered medicinal product, two kinds of PK analysis were conducted at all selected time points: by the total concentration of dornase alfa and after the first administration of the medicinal product net of the baseline level of endogenous dornase alfa.

Following the results of the open-label, prospective, multicenter, randomized comparative study of pharmacokinetics, clinical effectiveness, and safety of Tigerase (GENERIUM JSC, Russia) and Pulmozyme® (F. Hoffmann-La Roche Ltd., Switzerland) as part of combined therapy in patients with cystic fibrosis, it was found that:

- Medicinal product Tigerase is well-tolerated by healthy volunteers on multiple 2.5 mg dose inhalation.
- The intergroup comparison did not reveal statistically significant differences between volunteer groups I (Pulmozyme®) and II (Tigerase) in the incidence of AEs (p=0.200). All AEs, registered in the study: 1 (10.0%) in Group I (Pulmozyme®) and 9 (90.0%) in Group II (Tigerase) were mild. One AE in Group I (Pulmozyme®) (dysphonia) and one AE in Group II (Tigerase) (increased AST) were assessed by the Investigator as possibly related to the medicinal product and resolved without consequences. Other 8 out of 9 AEs (88.9%), registered in volunteers of Group II (Tigerase), mainly laboratory data, had a questionable causality to the investigational product.

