#### 3.2 Study Methodology

This study is open-label, prospective, multicenter, randomized, comparative, and parallel-arm.

According to the Screening results, , the patients who meet the inclusion criteria and are without the exclusion criteria will be randomized 1:1 to one of the treatment groups.

**Group I** is an active treatment group (50 patients), administered the medicinal product Tigerase (GENERIUM JSC, Russia) at a dose of 2.5 mg, once a day by inhalation for 24 weeks  $\pm$  1 week.

**Group II** is a reference group (50 patients), administered the medicinal product Pulmozyme® (F. Hoffmann-La Roche Ltd., Switzerland) at a dose of 2.5 mg, once a day by inhalation for 24 weeks  $\pm$  1 week.

An additional study of DNase sputum concentrations will include 24 patients from among the randomized patients (12 patients in Group I treated with Tigerase and 12 patients in Group II treated with Pulmozyme®). The DNase sputum concentration will be assessed once before the first inhalation and twice after the first inhalation of the study/reference product.

During the treatment, patients will be advised to continue the combined therapy that they received before enrollment to the study, including kinesiotherapy.

All patients enrolled in the study undergo the following successive **study periods**:

- **Screening/enrollment in the study** — for 21 days before the first administration of the study/reference product (3 weeks, Days from -21 to -1).
- **Randomization (Day 1)** — confirmed inclusion/exclusion criteria and patient allocation to one of 2 groups of therapy with a unique randomization number.
- **Therapy** — administration of the study/reference product for  $24 \pm 1$  weeks.

The duration of participation of each patient in the study, including the Screening period, will be about 28 weeks.

Upon the study completion, a final report containing the data on all patients enrolled in the study will be submitted to the regulatory authority in due course.

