## 9 TREATMENT PERIOD

### 9.1 Visit 2. Day 1. Randomization (Week 0)

A procedure of randomization will be performed at Visit 2. A unique randomization number will be assigned to each patient. Group I patients will receive the investigational product Tigerase, Group II patients — the reference product Pulmozyme®.

During participation in the study, the patients receiving Pulmozyme® as part of their standard medical service will be provided by the Sponsor with either investigational product Tigerase or reference product Pulmozyme® according to the randomization results.

At Visit 2, the following study procedures will be carried out:

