## **10.9 DNase Concentration Assessment**

The sputum DNase assessment of the patients who have agreed to participate in an additional study to assess the pharmacokinetics of the product will be performed once prior to the first inhalation and twice after the first inhalation of the study/reference product.

**Sputum samples** will be collected 1 hour  $\pm$  15 min before the inhalation of the study/reference product (*after the patient's randomization*), then 15 min  $\pm$  5 min and 1 hour 45 min  $\pm$  15 min after the end of inhalation (APPENDIX 1. Study Procedure Schedule).

Based on the individual data on DNase concentrations in sputum at each time point, following pharmacokinetic (PK) parameters will be calculated:

- $C_{\max}$  = maximum DNase concentration
- $T_{\max}$  = time to maximum DNase concentration

If necessary, other parameters may be calculated.

The assessment of DNase concentration in the sputum of the patients will be carried out in the specialized analytic laboratory. The procedure for collection, storage, and transportation of the sputum samples will be described in the laboratory guidelines that will be provided to the study centers. All essential data about biosample collection should be properly documented.

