### **Analysis of PK parameters**

Descriptive statistics will be provided for each PK parameter ( $C_{\max}$ ,  $T_{\max}$ ). A formal intergroup comparison, if necessary, will be carried out using a nonparametric Mann–Whitney test, since a significant deviation from the normal distribution is expected.

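### The PK set admits patients without any post-dose sputum sample, and the only named PK comparison, an optional Mann–Whitney test with 12 per arm, cannot support a conclusion of similar PK

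*Protocol*

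**What the plan says.** Section 3.2 describes an additional part in 24 of the randomized patients: "12 patients in Group I treated with Tigerase and 12 patients in Group II treated with Pulmozyme". Section 10.9 says that the sputum measurement "will be performed once prior to the first inhalation and twice after the first inhalation of the study/reference product". The nominal post-dose times are 15 minutes and 1 hour 45 minutes after the end of inhalation. Section 12.1 names two endpoints, Cmax and Tmax. Section 10.9 derives them from the concentrations at each time point and adds: "If necessary, other parameters may be calculated".

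Under Analysis populations, Section 15.1 builds the PK set from "patients for whom data were obtained at least at one time point of the PK measurement plan". Under Analysis of PK parameters it plans descriptive statistics and then: "A formal intergroup comparison, if necessary, will be carried out using a nonparametric" test, namely Mann–Whitney. No PK ratio, interval or margin is given.

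The title calls the trial a comparative study of pharmacokinetics. Objective 5 is to compare sputum DNase in the protocol summary, but to evaluate it in Section 2.

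**The concern.** The membership rule does not fit the endpoints. One of the three planned samples is taken before dosing, and the rule accepts any one of them. A patient with only that sample would enter with a Cmax that is a pre-treatment level and a Tmax before the dose. A patient with one post-dose sample would enter with a Cmax that cannot reflect the other time.

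The named test answers a different question from the one in the title. A Mann–Whitney p-value says whether a difference was detected. It does not say how large the Tigerase/Pulmozyme ratio is or which ratios remain compatible with the data. The product is presented as a biosimilar, so a non-significant result could be taken as evidence of similar exposure. No criterion is given for when the test becomes necessary.

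**Working it through.** **Which patients qualify.** The plan has three samples: one before the inhalation and two after it. Data at one point or more suffice, so any one of the three admits a patient, the pre-dose sample included. That patient has no post-dose value from which to take a treatment-related Cmax or Tmax.

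**Tmax.** With two nominal post-dose times, post-dose Tmax has two possible nominal values. It shows only which sample was higher.

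**What 12 per arm can show.** No SD, effect size or power is stated for the 24 PK patients, so there is no planned figure to reproduce. The inputs are:

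- n = 12 per arm (Section 3.2).
- Two-sided α = 0.05. The protocol states this for the primary endpoint; it is assumed here for PK.
- Lognormal Cmax with equal CV in both arms, CV assumed to be 30% to 100%. The only figures for orientation are the phase I plasma values in Section 1.3.2: 2.76/5.52 = 0.50 and 4.79/6.25 = 0.77.

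The formulas are:

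- Log-scale SD: σ = √ln(1 + CV²). For CV 50%: √ln(1.25) = 0.472.
- Expected 90% CI around an observed ratio of 1: exp(±t × σ × √(2/12)), with t = 1.717 on 22 degrees of freedom. For CV 50%: 1.717 × 0.472 × 0.408 = 0.331, giving 0.72 to 1.39.
- Ratio detectable with 80% power by a t-test on logs: exp(1.197σ). For CV 50%: exp(0.565) = 1.76.
- Mann–Whitney power: 4,000 simulated trials per cell. The simulation error is at most √(0.25/4000), about 0.8 percentage points.

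| CV | σ | Power, ratio 1.25 | Power, ratio 1.5 | Power, ratio 2.0 | 90% CI around 1 | Detectable ratio |
|---|---|---|---|---|---|---|
| 30% | 0.294 | 40% | 87% | 100% | 0.81–1.23 | 1.42 |
| 50% | 0.472 | 18% | 48% | 91% | 0.72–1.39 | 1.76 |
| 77% | 0.682 | 11% | 26% | 62% | 0.62–1.61 | 2.26 |
| 100% | 0.833 | 9% | 19% | 47% | 0.56–1.79 | 2.71 |

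A true 1.5-fold difference is missed in 13% of trials at CV 30% (100 − 87) and in 81% at CV 100% (100 − 19). Even at CV 30%, a 1.25-fold difference is missed in 60% (100 − 40).

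**Pre-dose level.** Section 9.1 concerns patients who receive Pulmozyme "as part of their standard medical service will be provided by the Sponsor" with one of the two study products. Section 8.2 tells them not to use their routine Pulmozyme before the Day 1 visit, but states no length of time. Carry-over into the pre-dose sample is therefore possible. Its size cannot be derived from the protocol.

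**The case against.** Several points on the other side stand. PK is an additional part in 24 consenting patients and is not the primary endpoint. Its planned analysis is descriptive, the test is conditional, and nothing in the protocol says that p > 0.05 will be read as similarity. PK patients are dosed in hospital on Day 1 and all samples fall within a few hours, so few should lack post-dose data. The phase I CVs are a weak proxy: they are plasma values in healthy volunteers whose levels did not reliably exceed endogenous ones, and they come from time-point means rather than individual peaks. The power figures are therefore a range under an assumption.

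Two stronger readings are tempting. A reader might infer that Cmax will be analysed without baseline correction. The protocol does not say so. A pre-dose sample is taken, other parameters are allowed, and Section 15.3 leaves analysis detail to a separate statistical analysis plan. The phase I precedent does not settle it either: Section 1.3.2 reports one analysis of total concentration and one "after the first administration of the medicinal product net of the baseline level of endogenous dornase alfa". A background common to both arms would pull the ratio towards 1, but the documents give no size for it.

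A reader might also infer that the PK question in the title cannot be answered at all. That goes too far, since the arms can be described side by side.

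It is also fair to say that a ratio with an interval does not make 12 per arm conclusive. Against limits of 0.80 to 1.25, used only as an illustration and not taken from the protocol, identical products would pass in about 17% of trials at CV 30% and about 0.1% at CV 50%. The interval makes that uncertainty visible; a p-value alone does not.

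None of this rescues the set definition, which is stated outright and does not match the stated endpoints.

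**Conclusion.** The point holds in a limited form. The stated PK set admits patients who have no treatment-related Cmax or Tmax. The only stated comparison gives no exposure ratio, and with 12 per arm a non-significant result cannot support PK similarity. Power for a 1.5-fold difference runs from about 87% to 19% over an assumed CV of 30% to 100%, with lognormal data, equal variability and two-sided α = 0.05. The 90% interval around a ratio of 1 runs from 0.81–1.23 to 0.56–1.79 over the same range. The sputum CV is not in the protocol, so where the trial falls in this range is unknown. Tmax adds almost nothing as a comparator. The primary endpoint is not affected.

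**What to change.** In Sections 12.1 and 15.1:

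- Require at least one post-dose sample for the PK set and both post-dose samples for Cmax, and derive Cmax from post-dose samples only.
- Report the Tigerase/Pulmozyme geometric mean ratio with a 90% CI at 15 minutes, at 1 hour 45 minutes and for Cmax. Working on the log scale also addresses the expected non-normality that the protocol gives as its reason for a rank test.
- Add a sensitivity analysis that takes the pre-dose level into account, either as a covariate or by subtraction with a stated rule for values that become zero or negative.
- Report Tmax descriptively only.
- State that p > 0.05 is not evidence of similar PK.
- Reconcile objective 5 between the protocol summary (compare) and Section 2 (evaluate).

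No extra samples or visits are needed. One or two patients with incomplete sampling may not contribute to Cmax, though a patient with one post-dose value still contributes at that time. The interval will be wide, and the report will have to say so.

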### **Analysis of the baseline characteristics of subjects**

To describe the baseline characteristics of subjects representing numerical variables (age, body weight, laboratory parameters, etc.), the following characteristics will be calculated:

- Number of nonmissing values (N)
- Arithmetic mean (M)
- Standard deviation (SD)
- 95% confidence interval (CI) for the mean
- Median (Med)
- Minimum (Min)
- Maximum (Max)
- Interquartile range (IQR)

The number and proportion of subjects will be provided for qualitative and categorical variables (sex, medical history, the incidence of abnormalities according to physical examination data, etc.).

A comparative intergroup analysis of the patient's baseline characteristics will be performed using the t-test (or Mann–Whitney test) for numerical data and using the  $\chi^2$ -criterion (or Fisher's exact test) for categorical variables.

### **Analysis of the primary efficacy endpoint**

When analyzing the primary efficacy endpoint (the change in FEV1 at Week 24  $\pm$  1 week from baseline), the data distribution will be preliminarily tested for normality using the Shapiro–Wilk test, as well as a test for symmetry and kurtosis. In the case of a normal distribution, the intergroup comparison will be performed using a t-test. If there are significant deviations from the normal distribution ( $p < 0.05$ ), a non-parametric Mann–Whitney test will be used. The null hypothesis for the equality of the FEV1 change on Week 24  $\pm$  1 week compared to the baseline between the two groups will be tested with a two-tailed test at a significance level of 0.05 using the Stata14 program. In addition, a 95% confidence interval will be calculated for the difference between the two groups. In addition, the generalized linear model (GLM) including sex, patient age, and medical history as covariates may be used to test the influence of different factors.

### **Analysis of secondary efficacy endpoints**

In this study, the planned secondary efficacy endpoints include the following:

- FVC change (absolute %) at Week 24  $\pm$  1 week from baseline (Screening);
- Number of chronic pulmonary disease exacerbations within 24 weeks  $\pm$  1 week of therapy;
- Number of days to a chronic pulmonary disease exacerbation over the period of 24 weeks  $\pm$  1 week of therapy;
- Body weight change at Week 24  $\pm$  1 week from baseline (Screening);
- Change in the average score on the subscales "Symptoms", "Activity", "Impacts", and the average total score of the St. George's Respiratory Questionnaire, version 2.2, at Week 24  $\pm$  1 week from baseline (Screening).

To analyze the change in FVC on Week 24  $\pm$  1 week versus baseline, a t-test or a Mann–Whitney test will be used, depending on the type of data distribution.

To analyze the number of chronic pulmonary disease exacerbations within 24 weeks  $\pm$  1 week of the therapy, Poisson regression is suggested. For each group of patients, the average number of exacerbations ( $M \pm SD$ ) recorded for 24 weeks  $\pm$  1 week will be presented. Subject's gender, age, FEV1 baseline (40–60% or more than 60% to 100% of the due value), presence of concomitant diseases, etc., can be used as covariates.

Additionally, the number and proportion of patients with one, two or three, or more exacerbations will be tabulated in total and by baseline FEV1 stratification. The intergroup comparison of these data will be performed by the  $\chi^2$ -criterion or Fisher's exact test (if the expected frequency in any cell is less than 5). The number of days to chronic pulmonary disease exacerbation will be analyzed using the Kaplan–Meier method, and also using the Cox regression model.

The intragroup analysis of body weight change at Week 24  $\pm$  1 week compared to baseline will be performed using the paired t-test or Wilcoxon test (with significant deviations from a normal distribution). The intergroup comparison will be performed using the t-test or Mann–Whitney test.

The data on change of the average score of the subscales "Symptoms", "Activity", "Impacts", and the average total score of the St. George's Respiratory Questionnaire, version 2.2, at Week 24  $\pm$  1 week compared to baseline will be analyzed using non-parametric methods: Wilcoxon test — for intragroup comparison and Mann–Whitney test — for intergroup comparison.

### **Analysis of PK parameters**

Descriptive statistics will be provided for each PK parameter ( $C_{\max}$ ,  $T_{\max}$ ). A formal intergroup comparison, if necessary, will be carried out using a nonparametric Mann–Whitney test, since a significant deviation from the normal distribution is expected.

### **Safety analysis**

The description of adverse events (AEs) will be presented according to the following scheme:

- Nature of the adverse event
- Severity of manifestation
- Duration
- Probable connection with the study substance
- Outcome

Adverse events will be coded in accordance with the Medical Dictionary for Regulatory Activities (MedDRA). The number, as well as the proportion of patients having developed a particular AE will be given for each AE/SAE. Intergroup comparison of categorical parameters (frequency of AE development, incidence of abnormalities based on results of physical examination, vital signs, laboratory and instrumental studies, patient diaries, and frequency of subjective complaints) will be carried out using the  $\chi^2$ -criterion or Fisher's exact test (if the expected frequency in any cell will be less than 5). The number and proportion of patients with any abnormalities will be given for each parameter.

Assessment of the quantitative parameters (vital signs and laboratory parameters, ECG data) over time by Week  $24 \pm 1$  week of treatment from baseline will be carried out using the Friedman test. If any statistically significant *post-hoc* differences are revealed, a pairwise comparison will be performed using the paired t-test or Wilcoxon test.

A generalized linear model (GLM) will be built to compare the dynamics of these parameters between the groups.

Data on the level of anti-drug antibodies against dornase alfa within 24 weeks  $\pm 1$  week of the therapy in patients of the active treatment group (Tigerase) and the reference group (Pulmozyme®) will be presented by means of descriptive statistics.

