### **4.2 Subject Exclusion Criteria**

1. Hypersensitivity to any medicinal product used in this study to its ingredients, as well as a history of significant, according to the Investigator, allergic reactions;
2. Acute respiratory infection or chronic pulmonary disease exacerbation within 4 weeks prior to Screening and on Screening with or without corticosteroid or antibiotic therapy;
3. Comorbidities and conditions that, according to the Investigator, endanger the patient's safety during his/her participation in the study, or which will influence the analysis of safety data if the disease/condition aggravates during the study, including:
  - ✓ Severe renal impairment (serum creatinine is more than 1.5 times higher than the upper limit of normal);
  - ✓ Severe hepatic impairment (the activity of alanine aminotransferase (ALT) or aspartate aminotransferase (AST) in the blood serum is 2.5 or more times higher than the laboratory upper limit of normal).
4. Lung transplantation in history or transplantation scheduled for the period of this study;
5. The presence of anti-HIV antibodies, active viral hepatitis B and/or C, and/or hepatic cirrhosis revealed in the history or identified during the Screening;

6. Pregnancy and breastfeeding;
7. Refusal of male and female patients with preserved reproductive function to use adequate contraceptive methods\* throughout the study and within 30 days after the end of the study/reference product dosing;
8. Patients who received blood or blood component transfusions 10 days prior to Screening;
9. Drug or alcohol abuse at the time of Screening or in the past, which, as to Investigator, makes the patient ineligible for the study;
10. Participation of the patient in any clinical studies and/or taking experimental medicinal product for 30 days before the Screening Visit.

\* This study considers the following as adequate methods of contraception:

- Sexual abstinence  
OR
- Any combination of the following two methods: male or female condom with spermicide, intrauterine device (IUD), diaphragm with spermicide, contraceptive sponge, or cervical cap with spermicide.

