## **10 STUDY PROCEDURES**

No study-related procedures will be carried out before the volunteer signs the Informed Consent Form. The volunteer will be given sufficient time to fully familiarize himself/herself with the objectives, upcoming study procedures, rights and responsibilities of the study subjects, the risks and benefits of participating in the study, and to discuss the study with family members and/or other physicians.

Below there are the procedures performed in this study. The Investigator should assess all clinical, laboratory, and instrumental tests results (normal values, clinically insignificant deviation, and clinically significant deviation).

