## 10.3 Physical Examination

Physical examination will be performed at the Screening Visit, during treatment on Day 1, Day  $7 \pm 2$  days, Day  $56 \pm 7$  days, Day  $112 \pm 7$  days, and Day  $168 \pm 7$  days in accordance with the Study Schedule (APPENDIX 1. Study Procedure Schedule) to verify the patient's physical parameters and deviations from them, assess the patient's state dynamics, and to reveal AEs/SAEs. Physical examination includes the evaluation of the patient's general condition and the condition of the following:

- skin
- visible mucous membranes

- musculoskeletal system
- subcutaneous fat and lymph nodes
- thyroid gland
- respiratory system
- cardiovascular system
- abdominal cavity organs
- urinary system organs
- sensory organs

Clinically significant differences from the initial examination findings should be regarded as AEs and reported accordingly in the source documentation and in the CRF. Clinically significant conditions revealed at the Screening will be recorded as medical history.

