### **13.2.13 Clinically Significant Deviations of Laboratory Parameters and Vital Signs**

Any clinically significant deviations in laboratory results found during or after the Screening should be attributed to the patient's medical history. After administration of the study or reference product, new or worsening clinically significant laboratory abnormalities should be reported as AEs in the original documentation and in the CRF.

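### The categorical abnormality tables in Section 15.1 make no reference to Screening, so unchanged long-standing findings count the same as new ones (minor)

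*Protocol*

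**What the plan says.** The Safety analysis part of Section 15.1 lists the categorical variables to be compared between arms. One is the "incidence of abnormalities based on results of physical examination, vital signs, laboratory and instrumental studies, patient diaries, and frequency of subjective complaints". The test is χ², or Fisher's exact test if an expected cell count is below 5. The paragraph ends: "The number and proportion of patients with any abnormalities will be given for each parameter". It sets no condition relative to Screening.

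The baseline part of Section 15.1 uses almost the same phrase, "the incidence of abnormalities according to physical examination data", for a baseline characteristic. Section 10 has the investigator place each result in one of three classes: "normal values, clinically insignificant deviation, and clinically significant deviation". These classes do not refer to an earlier result.

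The adverse event rules do use baseline:

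- Section 10.3 (examination): "Clinically significant differences from the initial examination findings should be regarded as AEs". Section 10.4 says the same for vital signs.
- Section 13.2.13 (laboratory): "new or worsening clinically significant laboratory abnormalities should be reported as AEs".
- Section 13.2.1.1: a pre-existing condition is an adverse event only if it changes.
- Section 10.7 (ECG): no explicit rule turns a change into an adverse event, although Section 13.1 names ECG as a source of adverse events.

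The Safety analysis also assesses quantitative vital signs, laboratory and ECG values over time from baseline (Friedman test) and compares their course between arms with a GLM.

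**The concern.** The tables name the variable and the test, and the variable as worded is presence. Some abnormality at entry is to be expected here: patients have chronic lung disease, with FEV1 admitted from 40% of the proper value. Section 4.2 excludes a patient only when "the activity of alanine aminotransferase (ALT) or aspartate aminotransferase (AST) in the blood serum is 2.5 or more times higher" than the upper limit, or when creatinine is more than 1.5 times that limit, so raised values below those levels are admitted.

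Findings carried over from Screening appear in both arms and tell nothing about the products. They pull the observed difference toward zero. In a biosimilar comparison, that is the direction that suggests comparable safety.

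**Working it through.** The protocol states no abnormality rate, effect size or power for these tables, so there is no figure of its own to reproduce. The calculation below is an illustration.

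**Inputs**
- 50 patients per arm (Section 3.2).
- χ², or Fisher if an expected count is below 5 (Section 15.1).
- Two-sided 0.05. The protocol states this for the primary endpoint only; it is assumed here.
- Assumed: b = share abnormal at Screening, equal in both arms and persistent.
- Assumed: q = rate of new abnormality among the rest, 10% (reference) and 30% (test).
- Assumed: w = rate of worsening among those already abnormal.

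**Formulas**
- Presence rate = b + (1−b)q, so the difference = (1−b)(0.30 − 0.10).
- New-or-worse rate among all patients = (1−b)q + b·w.

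Example, b = 20%. Presence gives 0.20 + 0.80 × 0.10 = 28% and 0.20 + 0.80 × 0.30 = 44%, a difference of 16 points. New findings only, among all 50 (w = 0), give 8% and 24%. That is also 16 points, but without the constant 20% that adds only noise. The ratio of the two rates is 3 instead of 44/28 = 1.6.

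Power by exact enumeration of two binomials under the plan's test rule:

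| b | Presence rates | Difference (points) | Power, presence | Power, new only, all 50 (w = 0) | Power, new only, those normal at Screening (n per arm) |
|---|---|---|---|---|---|
| 0% | 10 v 30 | 20 | 73% | 73% | 73% (50) |
| 20% | 28 v 44 | 16 | 39% | 62% | 63% (40) |
| 50% | 55 v 65 | 10 | 18% | 35% | 41% (25) |
| 70% | 73 v 79 | 6 | 11% | 11% | 16% (15) |

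If patients already abnormal worsen at the same rates at which the others become abnormal (w = q), the new-or-worse rates are 10% and 30% in all 50 at every b, and power is 73%. The gain from the recommended count therefore lies between the w = 0 column and 73%, depending on how much worsening occurs.

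**Sensitivity**
- Small b: at b = 5% with the same q, presence gives 62% and new findings among all 50 give 71%.
- Lower rates, q = 5% v 15%:

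| b | Presence | New only, all 50 (w = 0) | New only, normal at Screening | New or worse, all 50 (w = q) |
|---|---|---|---|---|
| 10% | 21% | 29% | 29% | 35% |
| 50% | 9% | 7% | 8% | 35% |
| 70% | 6% | 1% | 3% | 35% |

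Counting only new findings does not always give more power. With low rates and high b it does slightly worse than presence, though no count without worsening is then of practical use. This is why worsening should be included and patients abnormal at Screening kept in the denominator.

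**The case against.** **The analysis plan may settle this.** Section 15.3 defers the detailed procedure to a statistical analysis plan that is not shown, and definitions of treatment-emergent findings and shift tables often belong there. That has weight. But the protocol is not silent: it names the compared variable and the test, and an analysis plan would have to narrow that wording.

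**Incidence can mean onset.** A reader might infer that the protocol deliberately chose presence. The documents do not establish that. The baseline paragraph uses the phrase where onset on treatment is impossible, which points to presence, but it is one parenthetical example in a loosely worded translation. The fair reading is that the text leaves presence as its natural meaning and does not rule out onset.

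**Safety is also compared relative to baseline.** A reader might infer that any real safety difference would be diluted. The documents do not support that. New or worse clinically significant examination, vital-sign and laboratory findings enter the adverse event rates, which are compared between arms. The GLM compares change in quantitative values.

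**These tables are not free of open-label judgement.** It is tempting to call them the only comparison of abnormality rates that escapes it. Under Section 10 the investigator, who knows the treatment, classifies every result. The GLM on recorded values depends less on that judgement.

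**Phase I does not show a signal.** Section 1.3.2 reports 9 adverse events with the test product against 1 with the reference, mostly laboratory findings in the test arm. The comparison gave p = 0.200, all events were mild, and they were captured as adverse events, which is the route unaffected here.

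What stands is limited to the categorical tables. The GLM cannot cover physical-examination findings or an overall ECG conclusion. Deviations judged clinically insignificant do not become adverse events under Sections 10.3, 10.4 and 13.2.13, and Section 10.7 has no adverse event rule.

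**Conclusion.** The concern holds as a minor improvement to the categorical abnormality tables in Section 15.1. As written, they mix unchanged Screening findings with new ones, and the between-arm difference shrinks by (1−b). This assumes equal Screening prevalence in the two arms and persistence of the findings. Equal prevalence creates no systematic false difference; the cost is lost sensitivity.

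The amount cannot be stated, because the documents give no Screening prevalence and the exclusion limits cap severity without showing frequency. The power figures are illustrations on assumed rates. The tables are per parameter, so b may be small for many of them. Adverse event rates, the Friedman and GLM analyses and the primary FEV1 analysis are unaffected.

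**What to change.** In the Safety analysis part of Section 15.1:

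1. Make the compared variable an abnormality that is new or worse than at Screening, in line with Sections 10.3, 10.4 and 13.2.13. State the same for ECG.
2. Use as denominator all patients with a Screening assessment and at least one post-dose assessment of that parameter, not only those normal at Screening. The Day 1 examination and vital signs precede randomization (Section 9.1) and should not count as post-dose.
3. Add shift tables from Screening to the worst post-dose result. For laboratory values use the CTCAE v4.03 grade where one exists; Section 13.2.4 already uses that scale.
4. Keep the presence counts as descriptive tables, without a test.

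The schedule in Appendix 1 already collects Screening and post-dose results for these assessments, so no visits, samples or patients are added. The cost is wording and some programming. The drawback is smaller event counts, so Fisher's test will apply more often and, where few findings are new or worse, the tables will have little power.
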